### Secondary responder analyses at 6 weeks

We will conduct responder analyses to support clinical interpretation of treatment effects analysed on a continuous scale. Responders will include those who achieve a (1) ≥30% reduction from baseline in 24-hour cough frequency^31^; (2) ≥30 mm reduction from baseline on the CS-VAS^33^ and (3) ≥1.3-point improvement from baseline on the LCQ.^29^ We will analyse each responder outcome separately.

For each responder definition, we will report the proportion of responders by treatment group. Generalised linear models with an identity link will estimate between-group absolute risk differences and corresponding 95% CIs. These models will include treatment group and site as fixed effects. Where models fail to converge, risk differences will be estimated using alternative appropriate methods. Handling of missing data will follow the same approach as for the primary outcome.

### Sensitivity analyses

#### Testing the impact of protocol adherence

Anticipating that patients may discontinue treatment due to AEs, we will assess the robustness of the primary analysis at 6 weeks to deviations from the intervention protocol. This sensitivity analysis will occur with the primary outcome and select secondary outcomes in the per-protocol population.

For the morphine versus pregabalin comparison, the per-protocol population will include patients who received ≥80% of the intended study drug over the 6-week period. For the CCT versus no CCT comparison, the per-protocol population will include patients who (1) completed at least four out of the five weekly adherence diaries and (2) reported using at least one cough control strategy in three of those diary entries.

The same linear model or linear mixed-effects model described in the primary analysis will be applied to the per-protocol population.

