#### Cough control therapy

Patients assigned to CCT will attend five 45–60 min virtual sessions delivered by a trained physiotherapist or speech-language pathologist. The structure, based on prior literature^8
9
14^ and our group’s work,^17
18^ includes education, cough suppression strategies, breathing/laryngeal exercises and goal setting (table 2).

**Table 2 T2:** Summary of cough control therapy

Session	Week	Content
1	1	This session will focus on general education about chronic cough (ie, definitions, anatomy and mechanisms), introduction to cough suppression and goal setting. Participants will complete a baseline self-efficacy assessment using a combined measure consisting of the New General Self-Efficacy Scale^34^ and a brief, cough-specific self-efficacy scale developed for this study.^35^ Additionally, an entry interview will explore participants’ lived experiences with chronic cough and their expectations of the programme.
2	2	This session will focus on educating participants about cough triggers, behavioural sensitisation mechanisms and the benefits of non-pharmacological strategies. This session will also include the training and practice of 1–2 cough suppression techniques, with reinforcement of goal-oriented behaviour.
3	3	This session will cover the role of hydration, laryngeal hygiene and breathing exercises to control chronic cough.
4	4	This session will serve as a consolidation session, reviewing all aspects of cough control therapy and exploring the sustainability of the cough control strategies after the intervention.
5	6	This session will evaluate participants’ implementation of cough control strategies in daily life and their progress toward previously established goals. A final self-efficacy reassessment will be conducted, along with an exit interview to qualitatively explore participants’ experiences, barriers to maintenance and perceived impact of the therapy. Interview data will be analysed following a pre-specified protocol using reflexive thematic analysis.^36^

Participants will complete a weekly CCT diary asking them to reflect on the past 7 days and report: (a) how often they used cough control strategies (eg, urge suppression, breathing techniques); (b) in what contexts they applied these strategies (eg, at work, in public, while talking); (c) what barriers or facilitators influenced their ability to use the techniques and (d) the perceived effectiveness of the strategies scored on a 0–10 scale.

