### Study treatment adherence

We will assess adherence to morphine and pregabalin by self-report and tablet count. The physiotherapist and speech-language pathologist will evaluate adherence to CCT via the number of attended sessions and through weekly adherence diaries.^24^ For participants receiving the PRN bowel regimen, we will record the number of doses taken since the previous visit.

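### The per-protocol rule for cough control therapy (CCT) counts diaries and self-reported strategy use but not sessions attended, so it cannot detect missed therapy

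*Protocol article*

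**What the plan says.** Three places in the Protocol article bear on this.

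- **Cough control therapy** (under Study interventions) sets out the intervention: "Patients assigned to CCT will attend five 45–60 min virtual sessions delivered by a trained physiotherapist or speech-language pathologist". Table 2 gives each session its own content. The weekly diary asks, among other things, "how often they used cough control strategies (eg, urge suppression, breathing techniques"). None of its listed items covers attendance.
- **Study treatment adherence** says that the therapists will "evaluate adherence to CCT via the number of attended sessions and through weekly adherence diaries". Attendance is therefore collected, and it is one of two named adherence measures.
- **Testing the impact of protocol adherence** (under Sensitivity analyses) states that the per-protocol analysis checks robustness to departures from the intervention protocol. For CCT the rule has two conditions: "completed at least four out of the five weekly adherence diaries and (2) reported using at least one cough control strategy in three of those". The count of three thus applies to the diaries that the patient returned. For the drug comparison the set is "patients who received ≥80% of the intended study drug over the 6-week period".

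No other section adds an attendance condition to the CCT rule.

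**The concern.** The rule is complete, numbered and has cut-offs, so this is not a detail left to an unseen analysis plan. It uses one of the protocol's two adherence measures and leaves out the other, which is the direct record of whether therapy was delivered.

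Missing most of the sessions is the plainest departure from the CCT protocol, yet the rule has no means of seeing it. Failing to return two diaries is a lapse in data collection, yet it removes a patient whatever therapy was received. An unreturned diary is in effect scored as non-adherence.

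CCT versus no CCT is one of the two co-primary comparisons, and this is its adherence check. If the set is not tied to therapy received, the estimate cannot be read as the effect in patients who received the therapy, and agreement or disagreement with the intention-to-treat result says less than intended.

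**Working it through.** **Inputs from the protocol.** Five sessions; five diaries; at least four diaries completed; use reported in three of those diaries (read here as at least three). The protocol gives no attendance or diary-return rate.

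**Step 1: does membership depend on attendance?** Let s be sessions attended (0 to 5), d diaries completed (0 to 5) and u diaries reporting use (0 to d). The rule is: keep if d ≥ 4 and u ≥ 3.

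- Possible (d, u) patterns: 1 + 2 + 3 + 4 + 5 + 6 = 21.
- Qualifying patterns: d = 4 with u = 3 or 4 (two), and d = 5 with u = 3, 4 or 5 (three), so 5 of 21.
- s does not appear in the rule, so the same 5 patterns qualify at every attendance level from 0 to 5.

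**Step 2: three records put through the rule.**

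| Sessions | Diaries | Diaries with use | Per-protocol? |
|---|---|---|---|
| 1 of 5 | 4 | 3 | Yes |
| 5 of 5 | 3 | 3 | No (3 < 4) |
| 5 of 5 | 5 | 5 | Yes |

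The first record is possible because session 1 already introduces cough suppression (Table 2), so a patient could report using a strategy without the later technique training, breathing exercises or consolidation. These are cases that the rule allows; nothing shows that they are common.

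**Step 3: how often would a full attender fail on diary count alone?** Assume that each of five diaries is returned independently with probability p. Then

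P(fail) = P(X ≤ 3) = 1 − 5p⁴(1 − p) − p⁵.

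| p (assumed) | 5p⁴(1 − p) | p⁵ | P(fail) |
|---|---|---|---|
| 0.95 | 0.2036 | 0.7738 | 0.023 |
| 0.90 | 0.3281 | 0.5905 | 0.081 |
| 0.80 | 0.4096 | 0.3277 | 0.263 |
| 0.70 | 0.3602 | 0.1681 | 0.472 |

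**Step 4: what this means in patients.** Multiplying by the 62 patients planned for CCT gives about 1, 5, 16 or 29, but only if all 62 attend every session. Under an illustrative set of assumptions (mean attendance about 0.88 per session, mean diary return about 0.80 per week), roughly 51–53% attend all five. The number of full attenders lost on diary count is then about 6 to 9. The lower end applies when attendance and diary return are correlated within patients.

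**Step 5: how many near-non-attenders would be kept?** Under the same assumptions, with strategy use in 85% of returned diaries, patients with 0 or 1 session make up about 0.1–0.4% of the per-protocol set. Those with fewer than four sessions make up about 11%.

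**The case against.** The strongest reply is that the diaries are themselves a named adherence measure. CCT is a behavioural therapy whose techniques have to be used in daily life, and session 5 reviews exactly that. Defining adherence by enacted strategy use is defensible, and a drug and a behavioural therapy need not share one adherence metric. This stands: the diary criterion is not wrong, and the contrast with the drug rule is not in itself an error. What remains is that attendance, the other named measure, is absent.

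A reader might infer stronger things that the document does not support:

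- **That the set will be filled with patients who skipped therapy.** No adherence rates are given, and under the illustrative assumptions almost nobody with 0 or 1 session enters it. If attendance and diary return go together, the diary rule selects indirectly for attendance: about 20% of all patients attend fewer than four sessions in that scenario, against 11% of the set.
- **That 16 or 29 of 62 patients would be lost wrongly.** Those counts need every CCT patient to attend every session.
- **That attendance should replace the diaries.** A patient who attends four sessions and never uses a technique would then count as per-protocol, which is misclassification in the other direction.
- **That an attendance rule would remove bias.** Attendance is also a post-randomisation behaviour, as is taking at least 80% of the drug.

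The trial does not ignore attendance elsewhere: fidelity and session-by-session engagement are assessed separately, and attendance feeds the acceptability work described in the Discussion. None of that changes who enters the per-protocol set.

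**Conclusion.** The concern holds in a limited form. As written, membership of the CCT per-protocol set does not depend on sessions attended, so the analysis cannot detect one of the main departures that it is meant to test. This follows from the wording alone and needs no assumption.

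The size is unknown. The 2% to 47% range for a full attender failing on diary count rests on assumed, independent diary-return probabilities of 0.95 down to 0.7. It is an illustration, not a forecast.

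Severity is low. This is a supportive sensitivity analysis. The primary analysis is by intention to treat, and the sample size, the alpha split and the co-primary tests are untouched. Changing the rule would make the set match its stated purpose but would not turn the per-protocol estimate into a randomised comparison.

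**What to change.** In Testing the impact of protocol adherence, add a prespecified minimum number of attended sessions to the CCT-arm definition, for example at least 4 of 5 (4/5 = 80%, mirroring the drug rule), and keep the strategy-use criterion alongside it. State that an unreturned diary is not counted as non-use. One simple way to show its influence is also to report the set defined by attendance alone.

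The cost is a sentence or two and one extra sensitivity run, since attendance is already recorded under Study treatment adherence. The downside is a somewhat smaller set where both criteria apply.

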#### Testing the impact of including site as a random effect

To assess potential clustering by site, we will repeat analyses for the primary and key secondary outcomes using a model that treats site as a random effect. As site represents a stratification variable in the randomisation, we do not anticipate that site-level variation will meaningfully impact treatment effect estimates. However, this sensitivity analysis will account for any unmeasured heterogeneity across sites that may influence outcomes. We will compare estimates with those from the fixed effect model to assess any meaningful differences.

### Subgroup analysis

#### Testing whether the effect of CCT differs depending on neuromodulator treatment

Although not powered to detect interactions, we will conduct an exploratory subgroup analysis evaluating whether the effect of CCT differs depending on the neuromodulator treatment and vice versa.

Linear models will include fixed effects for site, CCT, neuromodulator treatment, their interaction and baseline log 24-hour cough frequency. Secondary outcomes with repeated measures will use mixed-effects models with participant-level intercepts and interaction terms as appropriate. If we observe evidence of a clinically meaningful interaction, treatment effects will be presented stratified by the interacting factor and conclusions will be interpreted accordingly. Interaction effects will be interpreted cautiously as exploratory.

#### Testing whether baseline self-efficacy impacts the effectiveness of CCT

Among participants receiving CCT, we will evaluate whether treatment effectiveness differs by baseline self-efficacy measured with the New General Self-Efficacy Scale (median split). Linear models for the primary outcome will include fixed effects for site, self-efficacy group (low vs high) and baseline log cough frequency. Secondary outcomes with repeated measures will use mixed-effects models with participant-level intercepts and interaction terms.

Post hoc contrasts will estimate the effect of CCT within each self-efficacy group (low vs high) at 6 weeks. These analyses will be exploratory with p values interpreted cautiously.

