### Sample size

We will enrol 124 patients and randomise them in a two-stage process. First, a 1:1 randomisation will assign patients to low-dose morphine or pregabalin (62 per group). Within each arm, a second independent 1:1 randomisation will assign patients to CCT or no CCT. This will result in four groups of 31 patients each. We powered the study on the 62-patient comparisons (ie, morphine vs pregabalin; CCT vs no CCT) rather than on individual groups. Because we anticipate a smaller effect size for the morphine versus pregabalin contrast, we conservatively based our sample size on this comparison.

The primary outcome is the change from baseline in natural log-transformed 24-hour cough frequency at 6 weeks. Assuming a 30% relative reduction in 24-hour cough frequency^31^ (corresponding to a mean difference of −0.357 units on the log scale), an SD in log coughs/hour of 0.6,^32^ and a 10% dropout, a total sample size of 124 participants (62 per intervention comparison) will provide 80% power at a two-sided alpha of 0.025. To maintain a family-wise type I error rate of 5% across our two co-primary hypotheses (morphine vs pregabalin and CCT vs no CCT), we applied a Bonferroni correction and set the significance level at α=0.025 for each comparison. We performed these calculations using the pwr.t.test function in the pwr package in R studio V.4.3.1 (Posit Software, PBC; Boston, MA, USA).

While our primary interest lies in estimating main effects, the factorial design also permits exploration of potential interactions between treatments. For the sample size calculation, we assumed no significant interaction—that is, that the effect of one intervention is consistent across levels of the other. Under this assumption, we will estimate the effect of morphine versus pregabalin by averaging across CCT and no CCT arms, and the effect of CCT versus no CCT by averaging across morphine and pregabalin arms.

To ensure sufficient participant enrolment, we will monitor recruitment at each site monthly and enact strategies (eg, additional sites) as needed to achieve the target sample size.

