#### Testing the effect of CCT on self-efficacy

Among participants receiving CCT, a linear model including fixed effects for site, time and baseline self-efficacy will assess changes on the New General Self-Efficacy Scale and the Cough Self-Efficacy Scale.

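### The exploratory self-efficacy analysis cuts the baseline score at the sample median; entering the score as continuous would keep information that the split discards, at almost no cost

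*Protocol article*

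**What the plan says.** Under the subgroup heading on whether baseline self-efficacy affects the effectiveness of CCT, the protocol article sets the question and the cut, among CCT recipients only: "we will evaluate whether treatment effectiveness differs by baseline self-efficacy measured with the New General Self-Efficacy Scale (median split"). The model is then fixed: "Linear models for the primary outcome will include fixed effects for site, self-efficacy group (low vs high) and baseline log cough frequency". Repeated secondary outcomes get mixed models with interaction terms, and contrasts are to give an effect of CCT in the low and in the high group. The section closes with a caveat: "These analyses will be exploratory with p values interpreted cautiously". It gives no reason for the cut and no analysis of the unsplit score.

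The next section, on the effect of CCT on self-efficacy, uses the same scale and mentions no split: "a linear model including fixed effects for site, time and baseline self-efficacy will assess changes on the New General Self-Efficacy Scale".

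Table 2, in the section on cough control therapy, places the baseline measurement in CCT session 1: "Participants will complete a baseline self-efficacy assessment using a combined measure consisting of the New General Self-Efficacy Scale". The article describes no such measurement in participants without CCT.

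**The concern.** A median split treats two patients just either side of the cut as opposites, and two patients far apart on the same side as identical. If response changes gradually with self-efficacy, the two-group comparison estimates that gradient less precisely than the score itself would. The cut also moves with the sample, so low and high have no fixed meaning outside this trial. The full score is evidently available, since the following section models it.

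What is at stake is modest. About 56 patients are evaluable, so precision is already limited, and a real association would be easier to miss. No primary, secondary or safety conclusion depends on this analysis.

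**Working it through.** **Inputs from the article.** Sample size section: "This will result in four groups of 31 patients each", so 2 × 31 = 62 patients on CCT; SD 0.6 on the log scale; 10% dropout. Study setting section: five sites.

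**The plan's own figure.** The article gives no power for the self-efficacy analysis. Its main-effect calculation reproduces: a two-sample t-test with difference 0.357, SD 0.6 and two-sided alpha 0.025 needs 55 per group (power 80.02%). 55 / 0.90 = 61.1, rounded up to 62 per group, or 124 in total.

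**Evaluable CCT patients.** 62 × 0.90 = 55.8, about 56.

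**Assumptions, because the article is silent.** Two-sided alpha 0.05; a linear relation between score and outcome; residual SD 0.6, borrowed from the sample size section; a range of slopes.

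**Information lost.** For a normal score, the squared correlation between the score and its median-split indicator is 2/π = 0.637. The loss is 1 − 0.637 = 0.363, about 36%, comparable to 0.363 × 56 ≈ 20 patients. By simulation the loss was 36% for a normal score, 36% for a discrete 8-item score, 26% for a uniform one and 43% for a skewed one.

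**Power by formula.** With five site terms, baseline cough frequency and the self-efficacy term, df = 56 − 7 = 49. The noncentrality is r/√(1 − r²) × √56, where r is the correlation of score and outcome; the split replaces r by r√(2/π). Example, r = 0.35:

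- Continuous: 0.35/0.937 × 7.483 = 2.80, power 78%.
- Split: r becomes 0.35 × 0.798 = 0.279; 0.279/0.960 × 7.483 = 2.18, power 57%.
- Loss: 21 points.

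The same formula gives a loss of 2 points at r = 0.1, 10 at 0.2, 20 at 0.3, 20 at 0.4 and 10 at 0.5.

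**Power by simulation.** Normal score, n = 56, 6,000 runs per slope. Slope is in log units per SD of self-efficacy, and r = slope/√(slope² + 0.36).

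| Slope | r | Continuous | Split | Loss (points) |
|---|---|---|---|---|
| 0.05 | 0.08 | 8% | 7% | 1 |
| 0.10 | 0.16 | 22% | 16% | 6 |
| 0.15 | 0.24 | 41% | 27% | 13 |
| 0.20 | 0.32 | 64% | 43% | 20 |
| 0.25 | 0.38 | 81% | 61% | 21 |
| 0.30 | 0.45 | 92% | 74% | 18 |
| 0.35 | 0.50 | 97% | 86% | 11 |
| 0.40 | 0.55 | 99% | 93% | 6 |

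Losses are taken before rounding. Across the four score shapes, for r from 0.2 to 0.4, the loss ran from about 7 points (uniform) to 25 points (skewed).

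**What these figures describe.** The primary-outcome model contains CCT recipients only and has no CCT term. Its self-efficacy coefficient says whether outcome differs by self-efficacy among treated patients. The power figures therefore concern that predictive association.

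**The case against.** The strongest objection is that the matter is small. The article labels the analysis exploratory and promises caution with its p values, and nothing in it proposes using the cut to select patients for CCT. That stands and keeps the point minor. Caution in reading a p value does not, however, recover the information that the split removed.

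A second objection concerns size. A reader might take a power loss of 13 to 21 points as a fixed property of the plan. The article does not support that: it gives no slope, score distribution or alpha for this analysis. Losses of that size arise only at moderate slopes, and at weak or strong slopes they are much smaller. The 36% likewise needs a normal score and a linear relation.

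A third concerns the question itself. A reader might infer that the split weakens a test of whether self-efficacy modifies the CCT effect, or that a continuous score would allow an interaction test in all randomised participants. Neither follows. The CCT-only model has no comparator, whichever form the score takes, and the article describes no self-efficacy measurement in no-CCT participants. Power figures for such an interaction would have no described data behind them. This objection stands in full: the missing comparator is the more basic limit of the section, and a continuous score does not cure it.

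Finally, the analysis plan summarised in online supplemental file 5 is not shown and might add an analysis of the unsplit score. That limits any claim that none is planned, but it does not remove the split that the article states.

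**Conclusion.** The point holds as a cheap improvement to an exploratory analysis. The article fixes a median split of a scale score without giving a reason, although the score is available. With a normal score and a linear relation the split discards about 36% of the information (26% to 43% under the other shapes tested). With about 56 evaluable CCT patients, residual SD 0.6 and two-sided 0.05, it costs about 1 to 21 points of power, most at slopes of 0.15 to 0.30 log units per SD. The slopes, alpha and score shape are assumptions. The finding applies to the association of self-efficacy with outcome among CCT recipients; the documents support no figure for modification of the CCT effect.

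**What to change.** In the subgroup section on whether baseline self-efficacy affects the effectiveness of CCT:

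- Replace the median split and the low/high term with the centred continuous baseline New General Self-Efficacy score, in the primary-outcome model and in the repeated-measures models with their interaction terms.
- Report the slope with its 95% CI. For readability, add model-based estimates at the 25th and 75th percentiles of the score.
- Check linearity with a plot or a quadratic term.
- Keep any low/high table as description only.
- Describe the result as an association between baseline self-efficacy and outcome within CCT recipients, and drop the wording that promises an effect of CCT in each self-efficacy group.

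The cost is a few lines of analysis wording, with no new data, visits or patients. The downsides are a linearity assumption and a result slightly less simple to present than two groups.

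### The self-efficacy subgroup analysis uses CCT recipients only, so it cannot estimate the CCT effect it promises within low and high self-efficacy groups

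*Protocol article*

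**What the plan says.** The Protocol article, under *Testing whether baseline self-efficacy impacts the effectiveness of CCT*, makes three statements in sequence.

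- Population and moderator: "Among participants receiving CCT, we will evaluate whether treatment effectiveness differs by baseline self-efficacy measured with the New General Self-Efficacy Scale (median split").
- Model: "Linear models for the primary outcome will include fixed effects for site, self-efficacy group (low vs high) and baseline log cough frequency".
- Quantity to be reported: "Post hoc contrasts will estimate the effect of CCT within each self-efficacy group (low vs high) at 6 weeks".

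Repeated-measures secondary outcomes get mixed models with interaction terms that are not specified further. The section calls these analyses exploratory.

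Table 2 (*Cough control therapy*) places the first measurement in CCT session 1, week 1: "Participants will complete a baseline self-efficacy assessment using a combined measure consisting of the New General Self-Efficacy Scale", together with a cough-specific scale. The reassessment is in session 5.

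The next section, headed *Testing the effect of CCT on self-efficacy*, reads: "Among participants receiving CCT, a linear model including fixed effects for site, time and baseline self-efficacy will assess changes".

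By contrast, the neuromodulator subgroup analysis just before these is set up with both factors: "Linear models will include fixed effects for site, CCT, neuromodulator treatment, their interaction and baseline log 24-hour cough frequency".

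**The concern.** The three statements on baseline self-efficacy cannot all hold. An effect of CCT is a comparison of CCT with no CCT, but the population leaves out every no-CCT patient and the model has no CCT term. What remains is a comparison of low with high self-efficacy among treated patients.

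If that comparison is reported under the promised label, ordinary prognosis may be presented as evidence that CCT works better in one kind of patient. Prognosis here means that patients with more self-efficacy may improve more, or less, whatever they are given. Such a result could influence who is offered CCT.

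The timing adds a difficulty. As Table 2 describes it, the score is taken after allocation in an open-label trial, so it may already reflect knowledge of the assignment. No collection in the no-CCT arm is described.

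**Working it through.** **Inputs.** From *Sample size*: 124 patients ("This will result in four groups of 31 patients each"), hence 62 on CCT; SD 0.6 on the log scale; 10% dropout; and a target effect "corresponding to a mean difference of −0.357 units on the log scale". From *Study setting*: five sites.

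**The plan's own figures.** ln(0.70) = −0.357, as stated. A two-sample t-test with d = 0.357/0.6, two-sided alpha 0.025 and 80% power needs 55.07, so 56 per group. Then 56 × 1.10 = 61.6, so 62 per group and 124 in total, as stated; dividing by 0.9 instead gives 63 and 126. The present point does not depend on this.

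**Can the CCT effect be estimated?** The stated model has an intercept, 4 site indicators, self-efficacy group and baseline: 7 columns. Adding CCT and CCT × self-efficacy makes 9.

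- CCT recipients only: rank 7 of 9. CCT equals the intercept, and CCT × self-efficacy equals self-efficacy group. Neither added term is estimable.
- All 124 patients: rank 9 of 9. Both are estimable.

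**What the CCT-only contrast contains.** Let π be the high-minus-low difference in outcome without CCT (prognosis), τ the CCT effect in the low group, and δ the extra CCT effect in the high group.

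- On CCT: high minus low = (τ + π + δ) − τ = π + δ.
- On no CCT: high minus low = π.

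Only the difference between these two lines gives δ. With the first line alone, π and δ cannot be separated, and τ does not appear at all.

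**Illustration.** The documents give no value for π, so these are assumptions. With δ = 0, a π of 0.10, 0.20 or 0.357 in absolute size is returned as 0.10, 0.20 or 0.357. If the low group does worse by those amounts, its cough rate is exp(0.10) = 1.11, exp(0.20) = 1.22 or exp(0.357) = 1.43 times that of the high group. Simulation (2,000 trials per row, 62 per CCT arm, even self-efficacy split, residual SD 0.6, site omitted) gives these mean estimates:

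| π | τ | δ | CCT-only contrast | All-patient interaction |
|---|---|---|---|---|
| −0.20 | −0.357 | 0 | −0.197 | −0.002 |
| −0.20 | 0 | 0 | −0.203 | −0.003 |
| 0 | −0.357 | −0.20 | −0.201 | −0.198 |

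The CCT-only analysis gives the same answer in all three situations.

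**Precision of an all-patient analysis.** Assume SD 0.6 and an even split, giving 31 per CCT-by-self-efficacy cell, or about 28 after 10% dropout.

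- CCT effect within one self-efficacy group: SE = 0.6 × √(2/31) = 0.152; with 28, 0.160.
- Interaction: SE = 0.6 × √(4/31) = 0.216; with 28, 0.227.
- Interaction detectable with 80% power at two-sided 0.05: (1.96 + 0.84) × 0.216 = 0.60, or × 0.227 = 0.64. That is about 1.7 to 1.8 times 0.357.

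**The case against.** **It is exploratory.** Self-efficacy is not among the listed primary, secondary or safety outcomes, and the plan promises caution with p values. This stands as a limit on the harm. It does not rescue the analysis: caution about p values deals with power and multiplicity, not with a quantity the model cannot produce.

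**The effect of CCT may mean change from baseline in CCT recipients.** That change also contains the neuromodulator effect, since every participant is randomised to a drug and drug is not in this model. It contains regression to the mean and time trends as well. The no-CCT arm exists to remove these. The interaction terms in the mixed models face the same limit, because without untreated patients they give only self-efficacy-by-time contrasts.

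**Control scores may exist.** A reader might infer from Table 2 that no-CCT patients are never measured. The documents do not establish that: the visit summary is in a supplement that is not shown. The secure statement is that the article describes no such collection. Even if scores exist, the analysis text confines itself to CCT recipients.

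**The section on change in self-efficacy.** A reader might infer that it fails in the same way. It does not. Its body promises only to assess changes among CCT recipients, which a before-after model can do; only its heading claims an effect.

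**The median split.** A continuous score would use more information, but dichotomising is a common exploratory choice and has no bearing on whether the CCT effect can be estimated.

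**An all-patient analysis would be imprecise.** True, and it should be stated openly. It is a reason to consider relabelling, not a reason to keep the present wording.

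**Conclusion.** The point holds as an error in the text of an exploratory analysis. From the population and model stated, the CCT effect within self-efficacy groups and its modification by self-efficacy are not identifiable. This rests on the design alone and needs no assumed effect size. The numerical illustrations do rest on assumed prognostic differences, and the standard errors rest on SD 0.6 and even splits.

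A reader might go further and infer that the CCT main comparison is compromised. The documents do not support that. The primary analysis, its error rate and the sample size of 124 are unaffected.

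**What to change.** Choose one of two changes to the baseline self-efficacy analysis.

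1. **Make the effect estimable.** Collect the New General Self-Efficacy Scale from all participants at the baseline visit, before randomisation. In all randomised patients, fit site, neuromodulator, baseline log cough frequency, CCT, self-efficacy and CCT × self-efficacy, and read the CCT effect at low and high self-efficacy from that model. The cost is a short extra questionnaire for everyone before allocation, including CCT patients now assessed at session 1, plus revised wording. The estimate will be imprecise (interaction SE about 0.22 to 0.23 log units), and the plan should say so. This must be settled before enrolment, because pre-randomisation scores cannot be recovered later.

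2. **Relabel.** Keep the CCT-only model, describe it as the association of self-efficacy with outcome among CCT recipients, and delete the sentence promising a CCT effect. The cost is wording only.

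Under either choice, retitle the following section as before-after change in self-efficacy among CCT recipients. Its present title can stay only if week-6 self-efficacy is compared between CCT and no CCT with adjustment for baseline, which requires both scales in both arms at baseline and at week 6.
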